### Interventions

7.7

Compared with the control group, the intervention frequency is only once. That is, when distributing the HPV self-sampling kit, the intervention group needs to prepay to obtain the kit, while the control group can receive the HPV self-sampling kit without payment. Considering that the market price of an HPV self-sampling kit is around 20 RMB, we set the prepayment fee at 20 RMB. This can well simulate the real situation when the participants purchase the kit by themselves in daily life. Moreover, a proper deposit can avoid the problems caused by a high deposit: ① exceeding the participants’ affordability and thus reducing their willingness to participate; ② increasing the participants’ psychological pressure and causing unnecessary worries, which may affect the accuracy of the study results. On the other hand, a proper deposit can also avoid the problems caused by a low deposit: lack of effective constraints, leading to participants not taking the trial seriously and thus causing unstandardized sampling operations and other problems that may affect the trial results. We use the deposit as an incentive to encourage participants to actively provide feedback on the results of HPV self-sampling and to increase the feedback rate of HPV self-sampling results. The intervention flow chart is shown in **Figure 2**. To enhance participants’ psychological commitment and ensure active participation, the full prepayment amount will be refunded upon completion and feedback of the self-sampling results. Participants can choose from various convenient payment methods, including cash, bank transfer, or third-party payment platforms, to minimize payment costs and barriers. After self-sampling, participants in the intervention group can return the sampling kit to the corresponding Maternal and Child Health Care and Family Planning Service Center, which will then forward it to the Genetic and Eugenics Office of the Inner Mongolia Maternal and Child Health Care Hospital. A dedicated hotline will be established to facilitate timely feedback from participants. For those with positive HPV results, free follow-up medical services, including physician consultations and examination appointments, will be provided to ensure they receive proper treatment. Additionally, ongoing monitoring of participants’ adherence to treatment will be conducted.

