### Control group

7.10

Participants will receive HPV self-sampling kits free of charge. Staff will provide a detailed explanation of the self-sampling procedure and precautions on-site and offer user manuals as well as video or illustrated guides to ensure that participants understand the correct self-sampling method. After completing the self-sampling, participants are required to send the samples to a designated laboratory for HPV testing. The study will cover all costs associated with sample transportation and testing, with no expenses incurred by the participants. Test results will be promptly communicated to participants via phone or text message. For those with positive HPV results, the study will provide information on follow-up diagnosis and treatment and referral channels to assist them in completing further medical examinations and treatment.

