#### Primary outcome

7.11.1

The primary outcome of this study is the feedback rate of HPV-based self-sampling. It refers to the percentage of participants who mail back the tested HPV sampling kits to us within 1 month after receiving the HPV self-sampling kits, relative to the total number of HPV self-sampling kits distributed. If the feedback is not received within 1 month after distribution, it is considered as no feedback by default.

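### The kit return route is described differently for the two arms, so a difference in return rate could not be attributed to the deposit alone

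*Protocol article*

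**What the plan says.** The protocol article, section 7.7 (Interventions), sets out the contrast at kit distribution: "the intervention group needs to prepay to obtain the kit, while the control group can receive the HPV self-sampling kit without payment". Section 7.2 defines the arms in the same way. Section 7.1 states the hypothesis as a higher feedback rate under prepayment, and the Discussion attributes the expected gain to the commitment that prepaying creates.

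On return of the kit, three places use three wordings:

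- Section 7.7: "participants in the intervention group can return the sampling kit to the corresponding Maternal and Child Health Care and Family Planning Service Center". The centre then forwards the kit to an office of the provincial hospital.
- Section 7.10 (Control group): "participants are required to send the samples to a designated laboratory for HPV testing".
- Section 7.11.1 (Primary outcome): the numerator is the women who "mail back the tested HPV sampling kits to us within 1 month" of receiving the kit.

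Other elements appear under one arm's heading only. Section 7.7 adds: "A dedicated hotline will be established to facilitate timely feedback from participants". It also says that for women with a positive result "free follow-up medical services, including physician consultations and examination appointments, will be provided". Section 7.10 says instead that "the study will provide information on follow-up diagnosis and treatment and referral channels". Section 7.10 alone describes on-site explanation, manuals and video or illustrated guides, and says that the study pays for sample transport and testing.

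**The concern.** Randomization balances the women. It does not balance procedures that are assigned along with the arm. If intervention women can hand the kit in locally and control women must send it to a laboratory, route and deposit are the same variable in the data, and no analysis of this trial can separate them.

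Most differences in procedure would matter little. This one matters because the primary outcome is itself the act of returning the kit within a month. Anything that makes return easier or harder moves the endpoint directly. The article's argument is about a deposit and its refund, and a result that mixes the deposit with the return route does not test that argument cleanly. This applies to a null result as well as a positive one.

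**Working it through.** **Step 1. The two arm descriptions side by side.**

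| Element | Section 7.7 (intervention) | Section 7.10 (control) | Tied to an arm by the text? |
|---|---|---|---|
| Payment | 20 RMB deposit, refunded | none | Yes, intended |
| Return route | local service centre, which forwards | send to a designated laboratory | Yes: 7.7 names the intervention group; 7.10 stands under the control heading |
| Hotline | mentioned | not mentioned | No: the sentence says participants in general |
| Sampling instruction, manuals, video | not mentioned | described | By heading only |
| Transport cost | not mentioned | covered by the study | By heading only |
| After a positive result | free consultations and appointments, adherence monitored | information and referral channels | By heading only; neither sentence names an arm |

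Return route is the one unintended difference that the text itself assigns by arm. The other rows rest on silence under one heading.

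**Step 2. Direction.** A local hand-in point and a hotline would, if they matter, raise intervention returns. Instruction and paid transport written only for controls would, if they matter, raise control returns. The text does not say that visiting a centre is easier than sending a sample at the study's expense. The net direction cannot be read from the document.

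**Step 3. Possible size.** The plan gives no figure on this point, so there is none to reproduce. Inputs from section 7.5: control rate 61.7%, intervention rate 90%, 54 women per arm, two-sided α = 0.05. Assumed: the deposit has no effect and non-deposit differences alone raise return in the intervention arm.

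Normal approximation, with p̄ the mean of p₁ and p₂ and n = 54:

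power = Φ{ [ (p₂ − p₁) − 1.96·√(2p̄(1−p̄)/n) ] / √[(p₁(1−p₁) + p₂(1−p₂))/n] }

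For p₁ = 0.617 and p₂ = 0.75: p̄ = 0.6835; the two standard errors are 0.0895 and 0.0886; (0.133 − 0.1754)/0.0886 = −0.48; Φ = 0.316. Summing the binomial probabilities exactly over all outcomes that the uncorrected chi-square test calls significant gives 0.320.

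| Assumed return rate, intervention arm | Gain over 61.7% | Chance of a significant result (exact) |
|---|---|---|
| 66.7% | 5 points | about 9% |
| 71.7% | 10 points | about 20% |
| 75.0% | 13.3 points | 32% |
| 80.0% | 18.3 points | 56% |

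The nominal rate with no difference is 5%.

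**Step 4. The opposite direction.** Suppose the deposit works as planned but the intervention arm loses 5 or 10 points because instruction or paid transport is given only to controls. Its rate is then 85% or 80% instead of 90%. By the same formula, power falls from 94% to 79% or 55%.

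**The case against.** The best defence is that this is a condensed article and that the two sections may describe different steps of one common procedure. The flowcharts, which may show the return path, are not available here. This is a fair reason not to treat silence as absence, and it disposes of several stronger readings that a reader might infer:

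- *That section 7.7 claims the arms differ only in payment.* It does not. The word *only* there qualifies how often the intervention is given; the next sentence contrasts the arms at kit distribution.
- *That the counted event differs by arm.* Section 7.11.1 gives one definition for everyone, and Table 1 names one source, laboratory records, with no split by arm. If arrival at the laboratory is what counts, forwarding time would work against the intervention arm.
- *That the hotline is for the intervention arm alone.* The sentence does not name an arm, and Table 1 lists an online consulting service at both time points without splitting it.
- *That follow-up care after a positive result is shown to differ.* The two descriptions differ, but the sentence in section 7.7 does not name an arm, and section 7.11.2.1 describes adherence tracking for participants generally. This care also comes after kit return, so it bears mainly on the adherence outcome.
- *That the bias favours the deposit.* Step 2 shows why this cannot be said.
- *That the trial could show nothing.* The effect of the whole package remains validly estimable.

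What the defence does not remove is the return route. The restriction to intervention participants is in the article's own words, and the control section states a different requirement. If the routes are in fact the same, the text is wrong; if they are not, the deposit is confounded with the route.

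**Conclusion.** The point holds for the return route. Followed as written, the protocol makes route and deposit coincide, on an outcome that is itself kit return, so a difference in return rate could not be attributed to the deposit alone. The direction of any distortion is unknown.

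Its size is also unknown. The range of about 9% to 56% for a significant result with an inert deposit rests on assumed gains of 5 to 18 points, none of which has support in the document. It shows what a moderate route effect could do and is not an estimate. The hotline and the care after a positive result are unclear wording that may apply to both arms, not demonstrated differences.

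**What to change.** 1. State for both arms the same return options (local centre, laboratory or both), the same transport cover, the same instructions and the same hotline, so that the prepayment and its refund are the only difference.
2. Define one dated event that counts as return in both arms, for example first receipt at a centre or laboratory within one month of distribution. Align sections 7.7, 7.10 and 7.11.1 with it, and reconcile it with laboratory records as the source in Table 1.
3. Reconcile sections 7.7 and 7.10 on what is offered after a positive result, so that the adherence comparison can be interpreted.

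The cost is protocol wording and minor changes to the instructions for the centres, which already take in returned kits. The drawback is that the control return rate may move away from the 61.7% used in section 7.5. These changes have to be made before data are collected, because the two effects cannot be separated afterwards.

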**Figure 2 f2:**
[figure not shown]
The intervention flow chart.

### “Pay-it-forward” collection process

7.8

Participants in the intervention group will pay a 20 RMB deposit before receiving the HPV self-sampling kit. This deposit serves as an economic incentive to complete the self-sampling and provide feedback. Staff will be trained on the collection process, record-keeping, and privacy protection. Payments will be accepted via WeChat and Alipay using QR code transfers. Each transaction will be recorded with participant details and verified daily against the number of participants and total amount received. Deposits will be held in a dedicated account, managed by a financial officer who will provide regular reports. Electronic receipts will be issued to participants. A supervisory committee will conduct regular checks to ensure transparency and compliance. In emergencies, collection will be paused, and funds will be securely stored for future refund.

### “Pay-it-forward” refund process

7.9

Participants will receive a full refund of their deposit after completing the HPV self-sampling and providing feedback. The project team will verify the feedback before initiating the refund process. Once approved, the refund will be processed by the financial officer and returned to the participant via the original payment method. Refund details will be meticulously recorded and verified by financial staff. Electronic refund certificates will be provided to participants. The supervisory committee will oversee the refund process to ensure transparency and compliance. In emergencies, refunds will be paused, and any unreturned funds will be refunded within one month after the study concludes.

### Control group

7.10

Participants will receive HPV self-sampling kits free of charge. Staff will provide a detailed explanation of the self-sampling procedure and precautions on-site and offer user manuals as well as video or illustrated guides to ensure that participants understand the correct self-sampling method. After completing the self-sampling, participants are required to send the samples to a designated laboratory for HPV testing. The study will cover all costs associated with sample transportation and testing, with no expenses incurred by the participants. Test results will be promptly communicated to participants via phone or text message. For those with positive HPV results, the study will provide information on follow-up diagnosis and treatment and referral channels to assist them in completing further medical examinations and treatment.

### Outcomes evaluation

7.11

#### Primary outcome

7.11.1

The primary outcome of this study is the feedback rate of HPV-based self-sampling. It refers to the percentage of participants who mail back the tested HPV sampling kits to us within 1 month after receiving the HPV self-sampling kits, relative to the total number of HPV self-sampling kits distributed. If the feedback is not received within 1 month after distribution, it is considered as no feedback by default.

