### Recruitment

7.3

Participants will be recruited at the Maternal and Child Health Family Planning Service Centers in four urban districts (Xincheng District, Saihan District, Huimin District, and Yuquan District) and five counties (Wuchuan County, Qing Shui He County, Helin County, Tuoketuo County, and Tuo Zuo Banner) of Hohhot City, Inner Mongolia Autonomous Region, China, starting from January 20, 2025.A multi-channel recruitment approach will be employed, including online WeChat public accounts, hospital outpatient clinics, and community health service centers. After identifying eligible and interested individuals, physicians at each Maternal and Child Health Care and Family Planning Service Center further explained the study objectives and procedures. Subsequently, eligible women were screened and selected based on predefined criteria. Each participant received a detailed informed consent form ((refer to Appendix), which outlined the study’s objectives, procedures, and potential implications. Women who reached mutual agreement and signed the informed consent form constituted the recruited cohort. Participants will be then randomly assigned to either the intervention group (“Pay-It-Forward” group) or the control group (“free”group).

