### Randomization

7.6

After completing the baseline study visit, participants were randomly allocated to one of the two study groups using a 1:1 ratio. The randomization procedure utilized a random number table approach. The detailed steps are as follows:

Random Number Generation: A basic randomization technique was employed. The study designer created a sequence of random numbers using the RANDBETWEEN function in Excel.Sealed Envelopes: These random number sequences were placed in identical, sealed, opaque envelopes that were sequentially numbered. Both the participants and the interveners are unaware of the participants’ group assignments.Enrollment Process: Upon enrollment of each participant, the researcher sequentially opened the envelopes in accordance with a predefined procedure.Assignment: Based on the number revealed in the opened envelope, the participant was assigned to the corresponding study group, and the researcher documented the assignment outcome.

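### Dividing the primary rate by kits distributed drops women who do not pay the deposit from the intervention arm only

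*Protocol article*

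**What the plan says.** The order of events is explicit in the protocol article.

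- **Randomisation comes first.** Section 7.3, after consent: "Participants will be then randomly assigned to either the intervention group" or the control group. Section 7.6: "After completing the baseline study visit, participants were randomly allocated to one of the two study groups using a 1:1 ratio".
- **Payment follows, in one arm.** Section 7.7: "the intervention group needs to prepay to obtain the kit, while the control group can receive the HPV self-sampling kit without payment". Section 7.8: "Participants in the intervention group will pay a 20 RMB deposit before receiving the HPV self-sampling kit".
- **Controls pay nothing.** Section 7.10: "Participants will receive HPV self-sampling kits free of charge".
- **The outcome is per kit.** Section 7.11.1 takes samples returned within one month "relative to the total number of HPV self-sampling kits distributed". Its rule for non-return also starts from the kit: "If the feedback is not received within 1 month after distribution, it is considered as no feedback by default".

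Two other places bear on the point. Table 1 describes the primary outcome as a percentage of participants and names no kit denominator. Section 7.2 describes 54 women obtaining kits by deposit and 54 obtaining them free. That presumes everyone pays and gives no rule for a woman who does not.

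**The concern.** An intervention woman who will not or cannot pay has no kit and no distribution date. She is outside the denominator, and the no-feedback default cannot reach her. No control woman can leave for this reason. Membership of the analysed group therefore depends on an event after randomisation that the intervention itself brings about.

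Two things are at stake. If women who decline the deposit are also less likely to return a sample, removing them raises the intervention rate with no change in anyone's behaviour. And whatever kind of women they are, the measure cannot show the main way a deposit could do harm, which is by putting women off taking a kit. The protocol knows of this mechanism: section 7.7 lists, as a problem of a high deposit, "exceeding the participants’ affordability and thus reducing their willingness to participate". The objective in section 7.1 compares the deposit with free distribution, so women lost at the payment step belong in the answer.

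**Working it through.** **Inputs.** From section 7.5: control rate 61.7%, hoped-for intervention rate 90%, 54 women per arm, two-sided α = 0.05. The share d of intervention women who do not pay is not given; it is assumed here to lie between 0% and 30%. The plan states no figure for this bias, so there is none to reproduce.

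**A. No true effect on behaviour.** Let 61.7% of women in each arm be women who would return a free kit, and let q be that proportion among refusers. The intervention rate per kit is then

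rate per kit = (0.617 − d·q) / (1 − d).

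Rejection probabilities are exact, from summing binomial probabilities for the uncorrected chi-square test, with 54 control kits and 54(1 − d) intervention kits, rounded to a whole number (51, 49, 46 and 43).

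*Extreme case, q = 0 (no refuser would have returned):*

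| d | Rate per kit | Spurious gain | Probability of p < 0.05 |
|---|---|---|---|
| 5% | 0.617/0.95 = 64.9% | 3.2 points | 0.066 |
| 10% | 0.617/0.90 = 68.6% | 6.9 points | 0.114 |
| 15% | 0.617/0.85 = 72.6% | 10.9 points | 0.215 |
| 20% | 0.617/0.80 = 77.1% | 15.4 points | 0.375 |

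*Middle case, q = 30.85% (half the control rate):*

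| d | Rate per kit | Probability of p < 0.05 |
|---|---|---|
| 10% | 65.1% | 0.067 |
| 15% | 67.1% | 0.090 |
| 20% | 69.4% | 0.126 |

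At d = 20%, the rate among all randomised women in this case is 0.694 × 0.80 = 55.5%. The arm looks 7.7 points better than control per kit while being 6.2 points worse as randomised.

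*Non-selective case, q = 61.7%:* the rate per kit stays at 61.7% and rejection stays near 0.05. The rate among all randomised women is 0.617 × (1 − d), which at d = 20% is 49.4%. A loss of 12.3 points is reported as no difference.

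**B. The planned effect.** If 90% is a rate per kit, the rate among randomised women is 0.90 × (1 − d). Power is from the normal approximation with 54 per arm against 61.7%:

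| d | Rate among randomised | Difference from 61.7% | Power |
|---|---|---|---|
| 0% | 90.0% | 28.3 points | 0.94 |
| 5% | 85.5% | 23.8 points | 0.81 |
| 10% | 81.0% | 19.3 points | 0.60 |
| 20% | 72.0% | 10.3 points | 0.20 |
| 30% | 63.0% | 1.3 points | 0.03 |

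The planned difference disappears at d = 1 − 0.617/0.90 = 31.4%.

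**The case against.** The strongest reply is that the two denominators are meant to be the same. Section 7.2 has 54 women per arm receiving kits, Table 1 speaks of participants, and section 7.11.1 itself opens with a percentage of participants, so the kit wording may be loose phrasing for the same 54. Refusal may also be rare: women consent before randomisation, the deposit is small and fully refundable, and section 7.7 offers 20 RMB as an amount that avoids the problems of a high deposit. Women may decline for reasons unrelated to whether they would return a sample. Finally, analysis sets are commonly left to an analysis plan.

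Part of this stands. The size of the bias is unknown, it is nil if everyone pays, and the q = 0 figures are the extreme end. Section 7.7 does not concede that 20 RMB deters anyone. Nor is the start of the one-month clock a serious asymmetry: payment takes place when the kit is handed over, so each woman has the same time with her kit.

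The rest does not remove the problem. Section 7.2 gives no rule for a woman who does not pay, and Table 1 adds a second reading of the primary outcome. Consent may lower refusal but cannot rule it out. An all-randomised analysis set in a separate plan would conflict with the denominator that section 7.11.1 names, so the definition itself has to change.

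**Conclusion.** The concern holds, and the definition must be corrected before analysis. As written, the sole primary outcome permits an exclusion after randomisation, in the intervention arm only, caused by the intervention. That conclusion follows from the protocol's own wording and needs no assumed figure.

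The size does need one. Across 5% to 20% refusal, the chance of a significant result when behaviour is unchanged runs from 0.066 to 0.375 if no refuser would have returned. At 20% refusal it is about 0.13 if refusers would have returned at half the control rate, and it is not inflated if refusal is unrelated to return. Even in that last case the measure conceals the women lost to the deposit.

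**What to change.** 1. In section 7.11.1, define the primary rate as samples received within one month divided by all women randomised to the arm.
2. State that a woman who does not pay, or who takes no kit for any reason in either arm, counts as no feedback.
3. Start the one-month window at randomisation or at the kit offer, identically in both arms, so that every randomised woman has a start date. This is a minor point beside the denominator.
4. Align Table 1 with the new wording.
5. Report, as supportive process measures, the deposit refusal rate, kit uptake by arm and the return rate per kit distributed.

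The cost is wording only. Section 7.6 already has every allocation documented and section 7.8 already has every payment recorded, so no further data are needed. The intervention rate may look less favourable. If the 90% in section 7.5 was meant per kit, power at 54 per arm should be restated on the new denominator.
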